# Integration of the Integrate, Design, Assess, and Share Framework in Developing the Environmental Health Literacy Toolkit Paraben-Free & Me: Protocol for a Randomized Controlled Trial

**DOI:** 10.2196/85474

**Published:** 2026-02-13

**Keywords:** educational toolkit, behavior, endocrine disruptors, knowledge translation, parabens

## Abstract

**Background:**

Endocrine-disrupting chemicals, such as parabens, are commonly found in personal care products (PCPs). Exposure to parabens is linked to several significant health risks, such as reproductive disorders, breast cancer, infertility, and hormone imbalances. Women are particularly vulnerable to these effects due to their higher use of PCPs containing parabens. Despite these risks, Canada lacks regulatory frameworks for the use of parabens in PCPs, relying instead on consumer awareness for reducing exposure. Previous studies have highlighted that many women remain unaware of parabens, exhibiting low risk perception and limited knowledge, which restricts behavior change toward safer choices.

**Objective:**

To address this gap, this project developed the Paraben-Free & Me educational toolkit using the integrate, design, assess, and share framework.

**Methods:**

Toolkit development methodology involved empathizing with target users, defining specific behaviors, grounding the data in the health belief model, ideating implementation strategies, prototyping, gathering user feedback, and building a minimum viable product.

**Results:**

The Paraben-Free & Me toolkit includes multimedia resources such as blog posts, interactive quizzes, videos, podcasts, and forums aimed at increasing knowledge, risk perceptions, and health beliefs and facilitating paraben-free behaviors.

**Conclusions:**

This toolkit shows potential to inform women about endocrine-disrupting chemicals, reduce exposures, and improve health outcomes.

## Introduction

Human exposure to endocrine-disrupting chemicals (EDCs) is widespread, as they can be found in electronics, pesticides, cosmetics, personal care products (PCPs), plastics, and other everyday products [1]. Parabens, for example, are a type of EDC commonly used as both synthetic preservatives and fragrance ingredients [2]. Women are at greater risk of exposure to parabens than men due to relatively higher PCP use, which has the potential to negatively impact their health and well-being [3-5]. For example, several studies have underscored the multifaceted impact of exposure to parabens and other EDCs, including the increased risk of pathophysiological reproductive conditions such as polycystic ovarian syndrome and endometriosis, breast cancer, infertility, and abnormal sex steroid hormone levels [2,3,6-9].

Compounding the negative impact of parabens is the lack of governmental restrictions and regulations for parabens and other EDCs in Canada. Unlike other regions, such as Europe, where there is a more robust approach to regulating EDCs [10], Canada uses a more risk-based strategy with no explicit regulation of EDCs [11]. Only products registered with Health Canada as natural health products have regulated limits on paraben concentrations [12]. By not implementing stricter regulations on parabens, the government of Canada puts the onus on the consumer to make health risk decisions.

Placing the burden on the consumer is concerning as, while there is increasing awareness of parabens and the associated negative health impacts, a large majority of women do not have a sufficient amount of knowledge about them [13-16]. To highlight this, a study by Trifunovski et al [16] conducted in Ontario, Canada, observed that women had low risk perceptions of parabens in PCPs, with 28% of participants having not previously heard of parabens. Additionally, increased knowledge, risk perceptions, and health beliefs were associated with an increase in women’s avoidance behavior [16]. Hence, if women do not possess information about parabens, it is difficult for them to implement changes to reduce their risk [13]. These findings highlight the importance of enhancing women’s knowledge and access to information, health beliefs, and risk perceptions to encourage paraben-free behaviors.

Hence, one such intervention that can be implemented to increase the awareness of parabens and, consequently, improve health outcomes is creating an educational toolkit. Educational toolkits are defined as a package of resources for knowledge translation and facilitating behavior change [17]. Toolkits typically include resources such as informational materials, checklists, guidelines, and interactive activities designed to educate and empower users. Studies have highlighted how toolkits can be used for behavior change [17,18]. A review by Barac et al [18] reported that, of the 31 included studies that evaluated toolkit effectiveness, 21 were found to be satisfactory or useful or resulted in an intention to change practice. However, there is no empirical evidence evaluating the effectiveness of a toolkit focused on parabens when used by women. To fill this gap, this paper aims to describe the methods for creating and developing an evidence-informed educational toolkit that facilitates paraben-free behavior.

## Methods

### Overview

The educational toolkit development and methodologies were guided by the integrate, design, assess, and share (IDEAS) framework for developing digital health behavior change interventions [19]. The IDEAS framework is made up of 10 stages: empathize, specify, ground, ideate, prototype, gather, build, pilot, evaluate, and share (Figure 1 [19]). The IDEAS framework aims to produce a digital intervention that integrates behavioral theory and user feedback [19]. This framework was selected due to its focus on human-centered design and iterative process. Therefore, by grounding the development of the educational toolkit in this framework, we can ensure that it is evidence-based and its efficacy can be evaluated.

The development of this toolkit began in November 2023 and included synthesizing previous research from members of our team to help inform the project, along with partnering with the Women’s Healthy Environments Network to aid with the development of this toolkit.

**Figure 1. F1:**

Stages of the integrate, design, assess, and share framework for developing digital interventions (reproduced from Mummah et al [19], published under Creative Commons Attribution 4.0 International License [20]). RCT: randomized controlled trial.

### Step 1: Empathize With Target Users

The first step was to empathize with target users to understand their needs and preferences [19]. An earlier project by Trifunovski et al [16] identified 6 EDCs commonly found in personal care and household products: parabens, bisphenol A (BPA), phthalates, tetrachloroethylene, lead, and triclosan. The study aimed to understand women’s current knowledge, risk perceptions, beliefs, and avoidance behavior related to these 6 harmful chemicals. A questionnaire was administered to 200 women to analyze associations between avoidance of parabens, BPA, phthalates, tetrachloroethylene, lead, and triclosan and knowledge, risk perceptions, and health beliefs [16]. Furthermore, 10 women living in Ontario, Canada, participated in virtual interviews to understand the factors that influence purchasing and avoidance behaviors.

### Step 2: Specify the Target Behavior

The goal of step 2 was to define the target behavior to be specific and measurable [19]. Mean knowledge, health belief, risk perception, and avoidance behavior scores from a previous study by Trifunovski et al [16] were used to calculate the appropriate group mean difference between the control and intervention groups. Using a Likert scale, participants’ knowledge and awareness, health beliefs, risk perceptions, and avoidance behaviors were evaluated through a composite score for each construct. For example, lower scores indicated lower knowledge and awareness. In this study, women scored an average of 21 (SD 6) points in the avoidance behavior section (scale from 6 to 30 in the original study). This step also included reviewing the current literature on educational toolkits to ensure that our toolkit was developed using best practices to elicit behavior change. Our research team conducted a comprehensive scoping review to answer the following research question: “What elements of educational toolkits contribute to improved risk perception and positive behavior change concerning the reduction of toxicant exposure from PCPs?” [21]. For this scoping review, we searched both academic studies and nonacademic literature, such as reviews of mobile apps that focus on PCPs, to ensure that we were able to analyze the literature surrounding educational toolkits that focus on increasing risk perception and promoting behavior change regarding harmful PCPs [21]. After the completion of this scoping review, and to further understand the aspects needed in an environmental health literacy toolkit, we also conducted a comprehensive systematic review to examine the current literature on environmental health literacy toolkits [22]. For this systematic review, we had two primary objectives:

To identify the characteristics of existing environmental health educational toolkits related to environmental health and behavior changeTo identify the methods and data collection tools used to evaluate the effectiveness of these educational toolkits

For our systematic review, we searched peer-reviewed published articles and gray literature, which includes research and information produced outside of traditional academic publishing sources. This includes government reports, policy documents, health service guidelines, internal organizational reports, technical briefs, professional association publications, conference abstracts, dissertations, and nongovernmental organization or charity publications. This review included gray literature to capture practical and context-specific information that is often unavailable in academic journals but is directly relevant to the development and implementation of the toolkit.

### Step 3: Ground in Behavioral Theory

The purpose of step 3 was to understand and use behavioral theories that could aid in the development of the educational toolkit [19]. The aim of this step was to ensure that each characteristic identified in steps 1 and 2 was grounded in theory. To achieve this, relevant behavior change theories were reviewed, and the health belief model (HBM) was selected as the primary framework due to its emphasis on individual perceptions, motivational determinants, and decision-making processes. The strategies and desired features found during steps 1 and 2 were evaluated for fit within the HBM, which focuses on explaining and predicting individual changes in health behavior.

### Step 4: Ideate Implementation Strategies

The team synthesized data and information that were gathered in steps 1 to 3 and developed concrete strategies to ensure that the toolkit was effective. This included brainstorming potential online platforms to build the toolkit, possible modes of delivery, and important characteristics to incorporate. Additionally, we worked on identifying key themes and mapping content to behavior change objectives. In partnership with the Women’s Healthy Environments Network, which is a nonprofit organization with the aim of educating the public and policymakers on environmental health, we ensured that our research was grounded in real-world insights.

### Step 5: Prototype Potential Product

The iterative process continued as the research team discussed the feasibility of implementing specific design ideas that were generated during step 4. We ensured that the features of the toolkit aligned with the focus of the literature, the theory, and the capabilities of the web-based platform.

### Step 6: Gather User Feedback on the Prototype

To gather user feedback, we gave our research team members (women aged 18-35 years) the opportunity to provide feedback on the first draft of our toolkit. The toolkit was emailed to the research team, and they were given 2 weeks to provide feedback.

### Step 7: Build a Minimum Viable Product

The final step was to build a functional toolkit for pilot testing. Modifications were continuously reviewed to ensure accuracy and adherence to prior steps of the process. The functionality of the toolkit was tested by the research team, with the focus being on ensuring a smooth user experience, which included a simple consistent layout, interactivity for users, and bright and accessible colors.

### Ethical Considerations

Ethics approval for this research was received from the Ontario Tech University Research Ethics Board on October 5, 2023 (17494). Informed consent to participate in this study was obtained from all participants. All participant-identifying details were omitted. No compensation was provided to the focus group, which consisted of members of the research team.

### Step 2: Specify the Target Behavior

This was promoting women’s paraben-free behaviors by increasing women’s knowledge and access to information, health beliefs, and risk perceptions using an educational toolkit that has been informed by the literature. Our hypothesis was that women who had access to the Paraben-Free & Me educational toolkit would exhibit a 10% improvement in paraben-free behavior (3.5 points), knowledge and access to information (3.5 points), health beliefs (2.5 points), and risk perception (2.5 points) in group mean difference scores when compared with those who did not have access to the toolkit.

Our scoping review of academic sources and users’ mobile app reviews revealed four themes of elements commonly observed in environmental health educational toolkits for facilitating behavior change: (1) toolkit accessibility and affordability, (2) simplicity of the presented information, (3) personalization of features, and (4) a clear focus on knowledge sharing [21]. This review highlighted not only the elements that are currently being featured in existing toolkits but also elements that users wish were included based on their reviews. Our systematic review highlighted the importance of toolkits being interactive, accessible, and personalized [22]. These factors were integrated into the development of our toolkit to ensure behavior change.

### Step 3: Ground in Behavioral Theory

The themes emerging from previous studies and the literature were aligned with the HBM [23] (Figure 2 [24]). This model suggests that an individual’s likelihood of adopting paraben-free behaviors is based on the individual’s perceived severity of disease, perceived susceptibility to developing diseases related to parabens, and perceived benefits of adopting the health behavior of using paraben-free PCPs [23].

This framework was selected as it emphasizes the psychological and social factors that shape health behaviors. It also provides guidance for designing educational health interventions as it highlights determinants of behavior change. Furthermore, research has underscored how there are positive associations between high knowledge, risk perceptions, and health beliefs and avoidance of lead, parabens, BPA, and phthalates [16].

Although a range of behavior change theories and frameworks, such as the capability, opportunity, and motivation–behavior framework; social cognitive theory; and the social ecological framework, offer valuable perspectives on the social and contextual determinants of behavior, this paper intentionally focuses on the HBM as the primary theoretical foundation for this project. This decision was guided by the aims of the toolkit, which center on addressing individual-level perceptions, decision-making processes, and motivational factors related to paraben-free behavior. Incorporating multiple frameworks risked diluting conceptual clarity and complicating the structure of the toolkit without clear added benefit for this specific application.

**Figure 2. F2:**
[figure not shown]
The health belief model of behavior change (reproduced from Fanwang0912 on Wikipedia [24] published under Creative Commons Attribution 4.0 International License [20]).

### Steps 4 and 5: Ideate Implementation Strategies and Prototype Potential Product

The research team summarized the data from previous steps and developed solutions to improve the toolkit. On the basis of these findings, we identified Wix as a suitable platform that provides tools for creating websites and mobile apps. Through this platform, the Paraben-Free & Me educational toolkit was created in the format of a mobile app. This platform was selected because it could be accessed anywhere and contained blog posts, forums, question-and-answer sections, video and podcast recommendations, and quizzes.

### Step 6: Gather User Feedback on the Prototype

Three users provided feedback to improve our toolkit. Feedback included design suggestions, such as including drop-down menus for blog posts and using smaller paragraphs. In terms of content, the users suggested that podcasts be included, as well as a larger number of videos. Suggestions were also provided on how often to update the toolkit, ranging from every 3 days to including a weekly summary message on Fridays.

### Step 7: Build a Minimum Viable Product

Through this design process, we built the Paraben-Free & Me toolkit, which included synthesizing previous literature, conducted by members of our research team, and sharing the first version of the toolkit with our research team (Table 1). The final version of the toolkit provides individuals with an array of resources to support learning. These resources include blog posts, quizzes, videos, and podcasts. We ensured that the posts had simple and consistent messaging, features that were highlighted in our systematic review, and incorporated constructs from the HBM (Table 2 and Figure 3A). To ensure that users were able to comprehend the material, we created built-in quizzes for users to test their knowledge on parabens and see what topics they may need to do more reading on (Figure 3B). Moreover, to build a sense of community, we also included a forum section for users to share their knowledge and provide them with the opportunity to recommend other resources or products (Figure 3C). Furthermore, additional resources, such as YouTube videos, documentaries, and podcasts, were included to support personalized learning (Figure 3D).

**Table 1. T1:** Identified characteristics, supportive feedback, and toolkit integration.

Theme	Feedback	Toolkit feature
Simple, consistent, and frequent messaging	Smaller paragraphs, buzzwords, and summarizing blog posts into short messages	Blog posts and weekly messages
Accessibility everywhere	—^a^	Mobile app
Health- and appearance-based motivators	—	Blog posts
Interactivity	Include checkpoints to interact with users	Forum page
Multimedia	Include audio and visual components	Blog posts
Personalization	Include audio and visual components and include additional resources to support different learning styles	YouTube videos, documentaries, and podcast recommendations
Incentives	—	Weekly quizzes

a Theme not discussed in the pilot-testing focus group.

**Table 2. T2:** Paraben-Free & Me intervention design.

Focus of instruction	Learning goal	HBM^a^ construct
“Parabens 101: What They Are and Why They’re Used in Cosmetics?”	Knowledge	Perceived severity and susceptibility
“The Truth About Parabens: What’s the Worst They Can Do?”	Risk perceptions	Perceived severity and susceptibility
“Can Switching to Paraben-Free Personal Care Products Improve Your Health?”	Health beliefs	Perceived benefits
“Are You Sure of What You’re Putting on Your Skin? Learn How to Check the Ingredients of Your Personal Care Products”	Knowledge	Perceived barriers
“How to Decode and Understand Product Labels and Websites for Healthier Choices”	Knowledge	Perceived barriers
“How to Identify Paraben-Free Personal Care Products and Make the Switch: Tips and Tricks for Healthier Shopping”	Paraben-free PCP^b^ behavior	Perceived barriers

a HBM: health belief model.

b PCP: personal care product.

**Figure 3. F3:**
[figure not shown]
(A) Example blog post featured in the Paraben-Free & Me toolkit to educate users on parabens, their health impacts, and how to avoid them. (B) Example of the weekly quizzes shared with users to test their knowledge and understanding of the blog post material. (C) Example forum page for users to share their knowledge and product recommendations. (D) One of the additional resources that users can access to support their learning.

## Discussion

### Principal Findings

Overall, the main purpose of this manuscript was to describe a case study of the application of the IDEAS framework to guide the process of developing a new toolkit designed to promote paraben-free behavior and increase women’s knowledge of parabens. Using the IDEAS framework allowed us to use an iterative design process that ensured that target users were able to provide feedback throughout the process. This ensured that the toolkit would work for the target population. The results from steps 1 and 6 provided important insights into the needs and preferences of the target population. These insights allowed the research team to make corrections and changes to the interactive toolkit during the design phase. In particular, gathering user feedback on the prototype (step 6) was extremely valuable as we were able to make modifications to ensure that the minimum viable product provided the target population with an array of resources.

### Comparison With Prior Work

Through the use of the IDEAS framework, we designed a toolkit that includes several desired features that are consistent with previous research focusing on toolkits. For example, in the focus group conducted to pilot-test the app, the use of videos and audio recordings was suggested to supplement the material presented in the blog posts to provide users with multimedia tools that may assist them in personalizing their learning. This suggestion is consistent with previous literature in which multimedia approaches and personalization of learning were used to increase knowledge and facilitate behavior change [21,22,25,26]. Additionally, the focus group highlighted the need for smaller paragraphs and summary messages at the end of the week. Simple, consistent, and frequent messaging is a common theme among educational toolkits in the literature [21,22,27].

### Future Directions and Implications

Following the IDEAS framework, the next step for this project will be assessing the effectiveness of the Paraben-Free & Me toolkit using a randomized controlled approach. This includes piloting the toolkit for potential efficacy and usability (step 8), evaluating the efficacy through a randomized controlled trial (step 9), and sharing the intervention and findings (step 10). A single-site study at Ontario Tech University will be conducted to measure the effectiveness of the toolkit among female students between the ages of 18 and 35 years, with half of the participants in the control group and half in the intervention group. The primary outcome of assessment will be paraben-free behavior, and secondary outcomes will include knowledge and access to information, health beliefs, and risk perceptions. Both groups will complete the questionnaire that assesses these outcomes at baseline and after the intervention period. Group mean differences and 95% CIs will be analyzed to determine whether there were differences between baseline and follow-up scores. Future iterations of the toolkit may include developing simple games, replacing weekly quizzes with daily morning quotes, and potentially adding incentives through gift vouchers or promotional codes for paraben-free products.

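### The stated analysis names no baseline adjustment although all four outcomes are measured at baseline in both arms; a baseline-adjusted between-arm model would settle the comparison and usually narrow the interval

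*Protocol article*

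**What the plan says.** The planned trial is described in one paragraph of the Discussion, under Future Directions and Implications. Allocation is equal: "with half of the participants in the control group and half in the intervention group". The outcomes are set out as follows: "The primary outcome of assessment will be paraben-free behavior, and secondary outcomes will include knowledge and access to information, health beliefs, and risk perceptions". On data collection: "Both groups will complete the questionnaire that assesses these outcomes at baseline and after the intervention period". On analysis there is one sentence: "Group mean differences and 95% CIs will be analyzed to determine whether there were differences between baseline and follow-up scores".

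The hypothesis stands elsewhere, in Results, Step 2. It is a comparison between arms: women with the toolkit "would exhibit a 10% improvement in paraben-free behavior (3.5 points" and stated amounts on the other three outcomes), and this is meant "in group mean difference scores when compared with those who did not have access to the toolkit".

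No model, covariate or change-score definition is named. The words raw and unadjusted do not appear either.

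**The concern.** The article does name an analysis, and that analysis can be read in three ways:

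- change from baseline to follow-up within each group;
- a between-arm comparison of change scores;
- a between-arm comparison of follow-up means.

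The first does not test the hypothesis in Results, Step 2, because change within the toolkit group alone does not separate the toolkit's effect from whatever would have changed without it. The other two do test it. Without a baseline covariate, however, each uses the baseline score less well than a model that lets the data set its weight: the change score fixes the weight at one, and the follow-up mean fixes it at zero.

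At stake is the width of the 95% confidence interval for the primary outcome and the three secondary outcomes, and whether the reported quantity is the one the hypothesis is about. The baseline data will be collected in any case.

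**Working it through.** **No figure to reproduce.** The article states no sample size, power or baseline-to-follow-up correlation. The variance ratios below need only the correlation ρ. The sample sizes that follow them are illustrations.

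**Which comparison.** The analysis sentence looks at differences between the two time points. The hypothesis in Results, Step 2, looks at differences between women with and without the toolkit. The two agree only if the analysis sentence is taken to mean a between-arm comparison, which it does not say.

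**Variance on each between-arm reading.** Take the same standard deviation σ at both time points and in both arms, correlation ρ, n per arm, and a linear relation with a common slope. The variance of the estimated difference is (2/n) × V, where

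- follow-up means only: V = σ²
- change scores: V = 2σ²(1 − ρ)
- ANCOVA: V = σ²(1 − ρ²)

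Hence ANCOVA / follow-up only = 1 − ρ², and ANCOVA / change = (1 − ρ²) / [2(1 − ρ)] = (1 + ρ)/2. Neither exceeds 1. The ratio of interval widths is the square root.

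| Assumed ρ | Variance ratio, ANCOVA / change | Variance ratio, ANCOVA / follow-up only | Width ratio vs change | Width ratio vs follow-up only |
|---|---|---|---|---|
| 0.2 | 0.60 | 0.96 | 0.775 | 0.980 |
| 0.3 | 0.65 | 0.91 | 0.806 | 0.954 |
| 0.5 | 0.75 | 0.75 | 0.866 | 0.866 |
| 0.7 | 0.85 | 0.51 | 0.922 | 0.714 |
| 0.8 | 0.90 | 0.36 | 0.949 | 0.600 |

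At ρ = 0.5 the interval is 1 − 0.866, or about 13%, narrower than under either alternative. Below ρ = 0.5 the change score is less precise than ignoring baseline, since 2(1 − ρ) is then above 1 (1.6 at ρ = 0.2).

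**Illustration in sample size.** Inputs: a difference of 3.5 points (Results, Step 2); SD 6 (Methods, Step 2, where "women scored an average of 21 (SD 6) points in the avoidance behavior section (scale from 6 to 30 in the original study")); two-sided 5% level, from the 95% interval; equal allocation; assumed 80% power; no dropout. By the normal approximation, follow-up only needs 2 × (1.960 + 0.842)² × 36 / 12.25 = 46.1, so 47 per arm. Multiplying 46.1 by 2(1 − ρ) or by 1 − ρ² and rounding up gives:

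| Assumed ρ | Follow-up only | Change | ANCOVA |
|---|---|---|---|
| 0.2 | 47 | 74 | 45 |
| 0.5 | 47 | 47 | 35 |
| 0.7 | 47 | 28 | 24 |
| 0.8 | 47 | 19 | 17 |

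At 47 per arm, power is 80.7% for follow-up only at any ρ. For change scores it is 60.9%, 80.7% and 95.5% at ρ = 0.2, 0.5 and 0.7. For ANCOVA it is 82.3%, 90.4% and 97.7%.

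**Limit of the illustration.** On the 6-to-30 scale, 3.5 points is 3.5/24 = 14.6% of the range, 3.5/30 = 11.7% of the maximum and 3.5/21 = 16.7% of the mean. None of these is the stated 10%. The trial's scale may therefore differ from the one on which SD 6 was observed. The variance ratios do not depend on scale; the sample sizes and powers do.

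**The case against.** The strongest objection is that the article is about building the toolkit, gives the trial one forward-looking paragraph, and may leave the model to a full protocol or analysis plan that is not shown. That stands as a limit: the absence of modelling detail would not be a finding by itself. The point survives because the article does state an analysis. The wording of that statement leaves the comparison open, and a better method is available from data it says will be collected.

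Second, ANCOVA also yields a mean difference between groups with a 95% confidence interval, so the sentence "Group mean differences and 95% CIs will be analyzed to determine whether there were differences between baseline and follow-up scores" is compatible with it. That also stands. A reader might infer that the plan commits to a raw, unadjusted comparison. The text does not say so, and its reference to baseline shows that baseline enters in some form. The loss of precision is therefore conditional on the analysis turning out to be unadjusted.

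Third, a reader might infer that chance imbalance at baseline would bias the result. Under randomization it does not: follow-up and change-score comparisons are both unbiased, and their intervals allow for chance imbalance. What remains is a shift conditional on the imbalance observed. With SD 6 and an assumed 47 per arm, the standard error of the baseline difference is 6 × √(2/47) = 1.24 points. At ρ = 0.5, an imbalance of that size moves a follow-up comparison by 0.5 × 1.24 = 0.62 points in its direction, and a change-score comparison by 0.62 points the other way. ANCOVA removes this, but it is part of the same gain in precision and not a separate defect.

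Fourth, the gain may be small: 4% of variance against follow-up means at ρ = 0.2, or 10% against change scores at ρ = 0.8. This is correct, and it is why a range is given.

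**Conclusion.** The point holds as a low-cost improvement. The article names no baseline adjustment although all four outcomes have baseline scores in both arms, and its analysis sentence does not say clearly that arms are compared. If the intended analysis is an unadjusted between-arm comparison, ANCOVA is at least as precise on either reading, apart from about one degree of freedom. Its variance is 0.60 to 0.90 of the change-score variance and 0.96 to 0.36 of the follow-up-only variance over assumed correlations of 0.2 to 0.8, and its interval is about 13% narrower than either at 0.5.

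The size of the gain in this trial cannot be fixed. The correlation and the sample size are not given, the unadjusted comparator is not known, and SD 6 comes from the earlier Ontario study's 6-to-30 scale. The ratios also assume equal variances at the two time points and a common linear slope. A reader might go further and conclude that the trial will test only change within groups. The literal wording permits that, but the between-arm hypothesis in Results, Step 2, speaks against it, so the fault is ambiguity and not a demonstrated wrong test.

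**What to change.** Replace the analysis sentence in Future Directions and Implications with a named between-arm model. The primary analysis would be a linear regression of the follow-up paraben-free behavior score on arm and the baseline score of the same outcome, reporting the adjusted intervention-minus-control difference with its 95% confidence interval. Knowledge, health beliefs and risk perception would each be analyzed in the same form, adjusted for their own baseline. If a full protocol or analysis plan exists, it should carry the same wording.

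The cost is one or two sentences and about one degree of freedom per outcome (for example, 91 residual degrees of freedom instead of 92 at 47 per arm). No new data are needed. The trial is described as still to be conducted, so the change can be made in advance of the data.
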